## Revision History

| Version | Date
(DD-MMM-YYYY) | Author                      | Summary of Changes |
|---------|-----------------------|-----------------------------|--------------------|
| Final   | 19-JAN-2024           | [name] | Initial version    |

## LIST OF ABBREVIATIONS

|             |                               |
|-------------|-------------------------------|
| CAD  | Coronary Artery Disease       |
| REML | Restricted Maximum Likelihood |
| RH   | Relative Humidity             |
| SAP  | Statistical Analysis Plan     |

## 1 INTRODUCTION

The purpose of this statistical analysis plan (SAP) is to present the statistical methodology that will be used for the final analysis of the combined data from the 2018-496 and 2019-2425 studies performed respectively in Sydney, Australia and Montreal, Canada.

## 2 STUDY DESCRIPTION

### 2.1 Study Design

The study took place at two sites (Montreal and Sydney). Study participants were asked to volunteer for 1 preliminary visit, 1 screening visit and 4 to 8 study visits. During the study visits, participants were to enter an environmental chamber maintained at either 38°C and 60% relative humidity (RH) (typical North American heatwave condition) or 45°C and 15% RH (typical Australian heatwave condition). For each study visit, the participants were to remain within the environmental chamber and rest in a seated position for 3 hours under various conditions (cooling strategies). In Montreal, the 6 study visits were the following:

- 1) 38°C and 60% RH, no intervention (control)
- 2) 38°C and 60% RH, with fan use
- 3) 38°C and 60% RH, with skin wetting
- 4) 38°C and 60% RH, with fan use and skin wetting
- 5) 45°C and 15% RH, no intervention (control)
- 6) 45°C and 15% RH, with skin wetting.

In Sydney, participants were recruited for 2 preliminary visits and the 4 experimental visits under the North American heatwave exposure with the various cooling strategies. They were also provided with the option of doing additional visits that would be carried under the Australian heatwave exposure with the 4 cooling strategies, resulting in 2 additional visits compared to Montreal:

- 7) 45°C and 15% RH, with fan use
- 8) 45°C and 15% RH, with fan use and skin wetting.

In Montreal, participants were to first undergo the 4 study visits for the simulated North American heatwave exposure to minimize attrition for the primary objective. Participants were subsequently to undergo the study visits for the simulated Australian heatwave exposure. Within each heatwave exposure (North American, Australian) the sequence under which participants would undergo the study visits was randomized. In Sydney, participants were to undergo the 8 study visits in a randomized sequence. Prior to each visit, participants were asked to refrain from strenuous physical activity, alcohol, and caffeine for 12 h. To ensure there is no carry-over effect, study visits were to be performed on separate days, with at least 72 h between visits. Participants prescribed calcium channel blockers were asked to withhold this medication for 48 hours prior to each study visit.

In Montreal, male or female participants aged between 50 and 80 years of age with stable coronary artery disease were to be included in the study. In Sydney, male or female participants aged 60 years or older were to be included in the study.

## **2.2 Study Objectives**

### **Primary objective :**

The primary objective of this study is to identify the optimal cooling strategy to alleviate cardiovascular strain of participants exposed to typical North American heatwave conditions (38°C with 60% RH). Cardiovascular strain will be quantified using rate pressure product, calculated as heart rate × systolic blood pressure. To address this objective, we will test the following hypothesis: During simulated heatwave conditions of 38°C and 60% RH, a control (no intervention) condition will result in a greater increase in rate pressure product compared to conditions of: fan use alone; skin wetting alone; fan use + skin wetting.

### **Secondary objective:**

A secondary objective is to identify the optimal cooling strategy to alleviate cardiovascular strain of subjects exposed to typical Australian heatwave conditions (45°C with 15% RH). Cardiovascular strain will again be quantified using rate pressure product.

### **Tertiary (exploratory) objectives:**

A tertiary objective is to examine if beta-blockers alter the effectiveness of cooling interventions during each simulated heatwave conditions. To address this objective, we will compare a group of CAD patients prescribed beta-blockers to a group of CAD patients not taking beta-blockers. To account for the potential confounding influence of calcium channel blockers, patients prescribed calcium channel blockers were asked to withhold this medication for 48 hours prior to each study visit.

Another tertiary objective is to evaluate how the cooling strategies affect thermal (such as core temperature and whole-body sweat rate), and perceptual responses (such as thermal comfort and thermal sensation).

## **3 DATASETS ANALYZED**

### **3.1 Full Analysis set**

The Full Analysis set consists in all eligible subjects who underwent the control study visit and at least one other experimental visit within the same heatwave exposure (see section 2.1).

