#### 4.7 Statistical Analysis:

The primary research outcomes for this study are rectal temperature (Tre), rate pressure product (RPP), heart rate (HR), blood pressure (BP), thermal sensation (TS), thermal comfort (TC) and pre to post trial whole-body sweat losses (WBSL). Secondary outcomes to be compared are skin temperature (TSk), limb blood flow (LBF), skin blood flow (SkBF), local sweat rate (LSR), cognitive performance, rating of nausea and light headedness (NL), and evidence of orthostatic hypotension (OH). All data will be compared between all four interventions and both conditions (very hot and dry, and hot and humid). To assess the primary and secondary outcome variables, pre to post trial changes as well as the means of the dependent variables will be analyzed using one-way repeated measures ANOVAs with the repeated factor of cooling intervention (four levels: no fan (NF), fan (F), fan and skin-wetting (FSW), and no fan and skin-wetting (NFSW)) will be employed. If significant main effects or interactions are found, independent differences will be assessed using a two-tailed paired Student's t-tests while maintaining a fixed probability (5%) of making a type I error using a Holm-Bonferroni correction. All statistical analyses will be performed with GraphPad Prism (version 6.0, GraphPad Software, La Jolla, CA).

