## **1- Introduction and definition of research problem**

Periods of extreme heat have been on the increase for several years now. In 2004, it was predicted that these climatic events would occur more frequently, be more intense and last longer. Periods of extreme heat can have catastrophic consequences for human health and well-being. The most striking example is the heatwave that hit Europe in 2003, causing the death of 70,000 people, including 40,000 in the space of 2 weeks. Since, many public health agencies have developed action plans to deal with periods of extreme heat, in recognition of the danger posed by such events.

Several studies have assessed the risk factors leading to hospitalisation and death during periods of extreme heat. It is now well established that the elderly are most at risk of hospitalisation and death during such events. However, it is important to consider that hospitalisations and deaths of elderly people during periods of extreme heat are not directly caused by excessive body hyperthermia (e.g., heatstroke). Rather, they are primarily driven by adverse cardiovascular events. These observations can be explained by the cardiovascular demands imposed by heat exposure. During heat exposure, vasodilation of cutaneous blood vessels promotes heat exchange between the body and the environment. However, this vasodilation results in a fall of peripheral resistance, which must be compensated for by an increase in cardiac output to maintain blood pressure. The cardiovascular demands imposed by heat exposure could exceed the ischaemic threshold of people with known or silent coronary artery disease, predisposing them to a risk of adverse cardiovascular events even if body temperature does not reach a level associated with, for example, heatstroke.

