## **2- Relevant literature review**

The devastating health impacts of extreme heat events are clear across the globe. For example, a heatwave caused 70 000+ excess deaths in Europe during the summer of 2003. Mortality/morbidity rates during heatwaves are especially elevated in people with coronary artery disease (CAD). A lower sweating capacity that occurs with ageing renders CAD patients more vulnerable to

overheating, potentially predisposing them to ischemic events in extreme heat. Risk may be further compounded in CAD patients prescribed cardio-selective beta-blockers, due to a blunted skin blood flow that may further compromise heat dissipation.

By far the most effective cooling strategy during a heatwave is air conditioning (AC) use. However, access to AC is not universal and economical concerns limit its use by those who do have access. Reliance upon AC also places significant burden on the electrical grid, which can cause brown-outs or black-outs during periods of extreme heat, and it adds a substantial thermal load to the environment. In contrast, electric fans offer a cooling strategy with a 50-fold lower power requirement (55-100 W vs. 1500-5000 W) and cost (\$64/year vs. \$850-\$2950/year) compared to AC. The energy benefits of this approach are two-fold: the individual is targeted instead of the surrounding space, and no active cooling of the air is required. During the 1990s, fan distribution programs targeted the most vulnerable in cities such as New York and Chicago as part of their heat wave management strategy. But these programs were discontinued due to concerns that fans paradoxically increase the risk of heat-related illnesses. In fact, all major public health agencies (e.g. WHO, CDC) now insist that fans should be turned off when ambient temperature exceeds  $\sim 35^{\circ}\text{C}$  because they can supposedly speed the onset of heat exhaustion and critically exacerbate dehydration. It should be noted that, despite such recommendations, a 2012 Cochrane review concluded there is no evidence to support or refute the use of electric fans during heatwaves.

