### *5.2.2 Exclusion criteria*

- Body mass index  $\geq 35 \text{ kg/m}^2$ .
- Currently undertaking estrogen therapy.
- Evidence of current fluid and electrolyte disorders, anemia, abnormal thyroid function, arrhythmias, renal disease, liver disease, cerebrovascular disease, significant pulmonary disease, endocrine abnormalities, significant cognitive impairment, psychiatric disorder, substance abuse, degenerative neurological condition or any other medical condition deemed to pose risk during the proposed experiments.
- Type 2 diabetes not controlled by medication and/or severe neuropathy and/or severe retinopathy and/or insulin therapy.
- Uncontrolled hypertension ( $>180/110 \text{ mmHg}$ ).
- Recent ( $<3$  months) coronary bypass surgery.
- Ejection fraction  $<40\%$  and/or clinical evidence/history of heart failure.
- Significant valvular heart disease
- Resting ECG abnormalities interfering with observation of ST segment changes during testing.

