## 4.2 Tertiary Efficacy Endpoints

The tertiary endpoints will be the change from baseline to the end of a 3-hour simulated heatwave exposure in: core temperature, whole-body sweat rate (whole-body sweat loss/duration of heat exposure), thermal comfort and thermal sensation.

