### 5.2 Efficacy Analysis

All efficacy analysis will be conducted on the Full Analysis set.

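### The SAP for the combined data plans no comparison of clinical harm by condition, and its only analysis set is unsuited to counting harm

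*Supplement*

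**What the plan says.** SAP section 1 states that the plan governs the final analysis of the data pooled from the two sites. Section 4 lists efficacy endpoints only: change in rate pressure product (RPP) and, at the tertiary level, "core temperature, whole-body sweat rate (whole-body sweat loss/duration of heat exposure), thermal comfort and thermal sensation". Section 3 defines one analysis set: "The Full Analysis set consists in all eligible subjects who underwent the control study visit and at least one other experimental visit", both within the same heatwave exposure. Section 5.2 adds: "All efficacy analysis will be conducted on the Full Analysis set". There is no safety set and no safety section. Under section 5.1, when an exposure ends before 180 minutes, the change is computed from the final reading obtained. No table of such exposures is planned.

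The latest Sydney protocol goes further. Section 4.6 has participants rate nausea and light-headedness and tick other symptoms every 15 minutes. It also takes blood pressure seated at the end of exposure and again after 1 and 3 minutes of standing. Section 4.7 includes among the secondary outcomes "rating of nausea and light headedness (NL), and evidence of orthostatic hypotension (OH". Neither outcome appears in the SAP, and no reason is given.

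**The concern.** The trial is meant to inform public advice on fans. The Montreal protocol (section 2) reports that agencies tell people to turn fans off above about 35°C because "they can supposedly speed the onset of heat exhaustion and critically exacerbate dehydration". Its section 1 adds that the cardiovascular demand of heat "could exceed the ischaemic threshold of people with known or silent coronary artery disease", and it describes the group's own pilot study, in which a fan increased strain in older adults at 42°C. A reader of the combined results will therefore ask whether any condition made people feel ill, lowered their standing pressure or led to more abandoned exposures. The SAP as written plans no answer.

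RPP does not fill the gap. It is heart rate times systolic pressure, so a fall in systolic pressure lowers it and, other things equal, looks like benefit. The standing readings are taken after the exposure ends and lie outside the endpoint.

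**Working it through.** **1. What the SAP can detect.** The documents' own power figure comes first (Montreal protocol, section 6.1: difference 1250 bpm × mmHg, SD of the paired difference 2000, two-sided level 0.05/3 = 0.0167, paired t-test, n = 30). The noncentrality is (1250/2000) × √30 = 3.42, and the exact noncentral-t power is 80.5%, which reproduces the stated 80%. The test is two-sided, so the same calculation applies to a rise in RPP with a fan. The numbers of participants below are assumptions:

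| Rise with fan | n = 45 | n = 75 | n = 90 |
|---|---|---|---|
| 1250 | 95% | 99.8% | >99.9% |
| 750 | 52% | 79% | 87% |

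Harm expressed as a higher RPP is thus well covered at the size that the plan calls clinically relevant. Core temperature is also compared with control, at the 0.05 level (SAP 5.2.3).

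**2. What the SAP cannot show.** Comparing the collected items with the planned analyses:

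- Nausea, light-headedness and other symptoms: collected in Sydney; absent from the SAP.
- Seated-to-standing pressure: collected in Sydney; absent from the SAP.
- Exposures ended before 180 minutes: absorbed into the endpoint through the final reading; not counted by condition.

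**3. How the set rule behaves for harm counts.** Take four visits at 38°C in random order and a participant who withdraws for good because of one of them. Membership of the set needs the control visit plus one other.

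If the fan-alone visit is the trigger and falls in position k, the participant is in the set only if control is among the k − 1 earlier visits. That has probability (k − 1)/3.

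- k = 1: excluded 100%
- k = 2: excluded 1 − 1/3 = 67%
- k = 3: excluded 1 − 2/3 = 33%
- k = 4: excluded 0%

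The average is (1 + 2/3 + 1/3 + 0)/4 = 50%.

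If the control visit is the trigger, only k = 1 fails the rule, so the average is 1/4 = 25%. Skin wetting alone and fan plus wetting behave like fan alone, at 50%.

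**4. Sydney's order.** SAP section 2.1 says that Sydney randomised all eight visits. Listing all 40,320 orders leaves the 38°C figures unchanged at 50% and 25%, because the four humid visits are still in random order among themselves. Some of these participants could still qualify through the hot-dry set. Exclusion from both sets is 37% for a trigger at the humid fan visit and 22% for a trigger at the humid control visit.

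**5. Illustration only.** No document gives a rate of fan-triggered withdrawal. If it were 2%, 5% or 10% of the 90 planned participants (56 + 34), that would be 1.8, 4.5 or 9 people. Half of them, about 0.9, 2.3 or 4.5, would be missing from the 38°C set.

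**The case against.** The strongest reply is that harm is not ignored. Control against fan alone is a named contrast in both heatwaves, tests are two-sided, and RPP and core temperature are the kind of measure on which the earlier pilot study saw a fan do worse (heart rate and core temperature). This stands. A reader might infer that a harm of fan use could not appear at all, and the documents do not support that.

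Second, an unfinished exposure is kept if the set rule is met, and a participant with a single visit gives no within-person contrast. This stands too, so the set is reasonable for efficacy. The difficulty arises only if the same set is used to count harm.

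Third, the Sydney protocol (section 4.7) still plans its own comparison of the two omitted outcomes, and the SAP does not withdraw it. The summary of changes also mentions a safety protocol that is not shown. So harms may be reported elsewhere. What remains is that the only plan for the combined data is silent, and that Sydney section 4.7 does not count early stops either.

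Two further readings are tempting but unsupported. One is that ST-segment change was dropped. It was never an outcome: it appears only in a Montreal exclusion criterion, "Resting ECG abnormalities interfering with observation of ST segment changes during testing", and nothing says that readable traces were stored. The other is to apply the exclusion percentages to the protocols' 20% and 10% dropout allowances. Those are general allowances, tied neither to harm nor to the time of leaving.

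**Conclusion.** The point holds for clinical harm, not for strain. The combined analysis would be silent on symptoms, orthostatic hypotension and early stops by condition, while a fan-related rise in RPP or core temperature could be detected. For counting harm, the analysis set loses on average twice as many fan-triggered as control-triggered permanent withdrawals (50% against 25%). These percentages assume random order, withdrawal immediately after the triggering visit and equal chance of each position. How many people this affects cannot be derived from the documents. The primary efficacy analysis is not called into question.

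**What to change.** Keep the Full Analysis set for efficacy. Add to SAP section 3 a safety set of every participant who entered the chamber at least once, analysed by the condition of each visit. On that set report, by condition, heatwave and site:

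- (a) the number of exposures stopped before 180 minutes, with the reason where it was recorded;
- (b) for Sydney, symptom ratings (with the summary named in advance, for example peak and end of exposure) and the seated-to-standing pressure change, each as a condition-minus-control difference with a confidence interval.

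If the sponsor prefers to leave (b) to a Sydney-only report, the SAP should say so. The cost is SAP wording and a few tables. The Sydney outcomes are already in that protocol, but they come from one site only, and the documents do not say whether reasons for stopping were recorded.

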## 6- Statistics

### 6.1 Sample size

The sample size computation is based on comparison of the primary endpoint (change in rate pressure product from baseline to the end of a 3 hour simulated heatwave exposure to 38°C and

60% RH) between the 4 conditions of control, fan use alone, skin wetting alone, fan use + skin wetting.

The mean and standard deviation of the change in rate pressure product were taken from the preliminary data presented in Figure 3 and are expected to range between 1000 bpm x mmHg and 1700 bpm x mmHg for the mean and between 1700 bpm x mmHg and 2000 bpm x mmHg for the standard deviation. The standard deviation of the difference between conditions is expected to be similar.

The main interest is to compare the control condition with the 3 other conditions taken individually, which implies a significance level of 0.0167 ( $0.05 / 3$ ). A difference of 1250 bpm x mmHg in change in rate pressure product between the control condition and any other condition is judged to be clinically relevant.

In this context a sample size of 30 participants will give 80% power to detect a difference of 1250 bpm x mmHg in change between the control condition and any other condition, assuming that the standard deviation of the difference between conditions is 2000 bpm x mmHg and using a paired t-test with a 0.0167 two-sided significant level. To account for an approximately 10% loss to follow-up rate, 34 participants will be included in the study. Of the 34 participants, 17 will be taking beta-blockers whereas the other 17 will not be taking beta-blockers.

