#### 5.2.1 Primary Analysis

The following descriptive statistics will be presented for the primary endpoint (change from baseline in rate pressure product) under the 38°C and 60% RH heatwave exposure: mean, standard deviation, median, Q1, Q3, minimum and maximum.

A restricted maximum likelihood (REML)-based linear mixed model including a term for condition and accounting for repeated measures, will be used to compare the change from baseline in rate pressure product under the 38°C and 60% RH heatwave exposure under the following conditions: control, fan alone, skin wetting alone and fan + skin wetting. Contrasts under this model will allow for the three main comparisons:

- Control vs. fan alone
- Control vs. skin wetting alone
- Control vs. fan + skin wetting

Differences between the control condition and each of the 3 other conditions will be tested and presented with point estimate along with 98.33% confidence intervals. These three comparisons will be tested at the 0.0167 significance level to control for the multiplicity of tests.

The assumption of normality underlying this model will be checked.

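### The Full Analysis set drops participants without a control visit, or with only one visit, whose data the planned REML models could use; the loss is small and the direction of any bias is not fixed

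*Supplement*

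**What the plan says.** SAP 3.1 admits "all eligible subjects who underwent the control study visit and at least one other experimental visit within the same heatwave exposure". SAP 5.2 then states: "All efficacy analysis will be conducted on the Full Analysis set". No other analysis set is defined, and no analysis of all available visits is planned.

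The primary model in SAP 5.2.1 is "A restricted maximum likelihood (REML)-based linear mixed model including a term for condition and accounting for repeated measures". It yields three contrasts, each against control, and "These three comparisons will be tested at the 0.0167 significance level to control for the multiplicity of tests". SAP 5.2.2 uses the same kind of model and the same three contrasts at 45°C. SAP 5.2.3 to 5.2.5 extend it to beta-blockers, sex, site and season.

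On visit order, SAP 2.1 describes randomisation within each exposure in Montreal, and for Sydney: "In Sydney, participants were to undergo the 8 study visits in a randomized sequence". Under SAP 5.1 a visit cut short still counts, through its last available measurement. The latest Montreal protocol (6.1) allows for about 10% loss (34 enrolled), and the latest Sydney protocol (sample size section) for about 20% (56 enrolled).

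**The concern.** The protocols planned repeated-measures ANOVA. The SAP moved to REML mixed models, one advantage of which is that people with incomplete visits contribute what they have, validly so when drop-out depends only on values already observed. SAP 3.1 gives part of that advantage away. A participant with two or three cooling visits but no control visit is removed, and so is one whose only visit in the exposure was control.

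Two things are at stake. The first is precision. The second is the missing-data assumption: because order is random, whether someone who stops early stays in the set depends on whether control, plus one other visit, came before stopping. If stopping is related to the responses seen so far, the set is selected on outcome, and the model cannot correct for people who are no longer in the data.

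**Working it through.** **Plan's own figure.** Montreal protocol 6.1: "a sample size of 30 participants will give 80% power to detect a difference of 1250 bpm x mmHg", "assuming that the standard deviation of the difference between conditions is 2000 bpm x mmHg", paired t-test, two-sided 0.05/3. The noncentral t distribution with 1250/2000 = 0.625 gives 80.5% at n = 30 and 78.7% at n = 29. Inflation: 30/0.90 = 33.3, so 34. Both figures reproduce. At n = 75 the same test has 99.8% power, so the pooled trial's power is not in doubt.

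**How many are excluded, by hand.** Planned loss is (34 - 30) + (56 - 45) = 15 of 90, or 16.7%. An assumed 6% drop-out after each of visits 1 to 3 of an exposure matches this: 1 - 0.94³ = 16.9%. With random order, a person who has done k of the 4 visits lacks control with probability 1 - k/4.
- Stop after 1 visit: 0.060; after 2: 0.94 × 0.06 = 0.0564; after 3: 0.94² × 0.06 = 0.0530.
- No control: 0.060 × 0.75 + 0.0564 × 0.50 + 0.0530 × 0.25 = 8.6%.
- Control only: 0.060 × 0.25 = 1.5%.
- Excluded: 10.1%, about 9 of 90. Of these, 0.0564 × 0.50 + 0.0530 × 0.25 = 4.1%, about 4 people, have two or three cooling visits.

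**Effect on the contrasts.** Large-sample simulation of the four-visit randomised crossover, 400,000 participants per setting. The fit was generalised least squares with a random intercept and known variances, standing in for REML. Assumptions not in the documents: SD 2000 per condition and within-person correlation 0.5, so the SD of a difference is 2000 × √(2 × 0.5) = 2000, as in the protocol; control mean 1700; and the drop-out models. After a visit with response y, the chance of stopping is 1/(1 + exp(-(y - 4500)/700)) for 'after high' and 1/(1 + exp((y + 1500)/700)) for 'after low'. In the last two rows, control alone is skipped according to its own unseen value. The contrast is strategy minus control, so negative favours the strategy. First contrast shown; simulation error about 3 to 4 units.

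| Missing visits | True effect | Excluded | All visits | SAP 3.1 set | SE ratio (SAP set / all visits) |
|---|---|---|---|---|---|
| Completely at random | -1250 | 10.1% | -1253 | -1252 | 1.011 |
| After high response | -1250 | 8.9% | -1252 | -1244 | 1.010 |
| After high response | 0 | 17.7% | -3 | -35 | 1.019 |
| After low response | -1250 | 26.1% | -1254 | -1175 | 1.029 |
| After low response | 0 | 13.5% | -6 | +20 | 1.014 |
| Control skipped, would be high | -1250 | 11.7% | -1018 | -1064 | 1.023 |
| Control skipped, would be low | -1250 | 12.5% | -1491 | -1441 | 1.024 |

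With correlation 0.3 or 0.7 (completely random and after-high settings, true effect -1250) the SE ratio is 1.007 to 1.013.

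**Fan truly worse than control.** The Sydney protocol hypothesises this for the hot, dry condition, and the Montreal protocol expects it at 46°C. With drop-out of about 6% per visit rising with the last response, and a true fan penalty of 700 to 1250, the SAP set moved the fan contrast 6 to 58 units in the fan's favour. The all-visits fit stayed within -4 to +7 of the truth.

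**Scale.** The largest shift in the table is 1254 - 1175 = 79, and 79/1250 = 6.3% of the relevant difference; 58/1250 = 4.6%. Excluding 10% of people costs only 1.011² - 1 ≈ 2% in variance, because those removed carry mostly indirect information on control contrasts.

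**The case against.** The set matches the planned contrasts. All are against control, Montreal was sized on a paired comparison with control, and someone without control gives no direct within-person information on any of them. The rule is not a completers-only rule either: control plus any one strategy suffices, and a shortened visit counts. All of this stands, and it explains why the loss of precision is so small. It does not explain why usable visits should be removed from a model that can weight them properly.

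A reader might infer that the rule tilts every control contrast towards the cooling strategies, because someone who stops after a bad cooling visit before reaching control is removed. The documents do not support that. They report neither how many participants lack control nor why. The rule cuts both ways: a person who stops after a bad control visit that came first is also removed, and one who stops after a bad cooling visit with control already done is kept. In the table the shift is nil, towards cooling or against it, depending on the mechanism and the true effect.

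Two further objections stand. When control is skipped because of its own unseen value, both fits are wrong and the SAP set is nearer the truth (off by 186 rather than 232, and by 191 rather than 241), so the gain from using all visits rests on drop-out depending on observed values. And at 45°C, fan visits exist only at Sydney while the two sites recruit different populations, so bringing in more between-person information needs a site term.

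**Conclusion.** The point holds as a minor one that is cheap to mend. SAP 3.1 discards visits that the REML models can use, at a cost of about 1-3% in the standard error of a control contrast. About 9-18% of participants are excluded in most settings; the 26% row goes beyond planned loss.

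It also relies on a stronger missing-data assumption than the model needs. Where drop-out depends on observed responses, the contrasts can move by roughly 0-80 bpm x mmHg, while the all-visits fit stays close to the truth. That range belongs to the mechanisms assumed here and is not a ceiling. Nothing is biased if visits are missing completely at random, and no sign can be assigned in advance. The case most worth guarding against is a truly harmful fan at 45°C with drop-out after high responses, where the penalty would be slightly understated. None of this would overturn a difference of 1250.

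**What to change.** In SAP 3.1, define the Full Analysis set for each exposure as all eligible randomised participants with an evaluable change in rate pressure product (a baseline and at least one in-exposure reading) at one or more visits of that exposure, whether or not the control visit was done. Fit the planned REML models of 5.2.1 to 5.2.5 on it. Include a site term at 45°C, because fan visits exist only at Sydney. Keep the present set as a sensitivity analysis, and report how many participants the present rule would exclude, with reasons.

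The cost is a reworded definition, one added model term at 45°C and a repeat run on the present set. The downside is slightly more reliance on between-person information from people with one visit or no control; comparing the two sets would show whether that matters.
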